### **7.4.2. Special Treatment Considerations**

#### **7.4.2.1. Premedication for Infusions**

Premedication for the infusions is not planned. However, if an infusion reaction occurs, appropriate medication may be used as determined by the study investigator(s). If infusion reactions are observed, but review of the data suggests that dose escalation may continue, administration of acetaminophen, 500 to 1000 mg and/or an antihistamine may be administered orally 30 to 60 minutes prior to the start of infusion for subsequent subjects.

The decision to implement premedication for infusions in subsequent cohorts will be made by the investigator and sponsor and recorded in the study documentation, along with the dose-escalation decision.

Any premedications given will be documented as a concomitant therapy (see Section 7.7).

#### **7.4.2.2. Management of Infusion Reactions**

There is a risk of infusion reaction with any biological agent; therefore, all subjects should be monitored closely. Symptoms and signs that may occur as part of an infusion reaction include, but are not limited to fever, chills, nausea, headache, bronchospasm, hypotension, angioedema, throat irritation, rash, pruritus, myalgia, and dizziness. In the event that a significant infusion reaction occurs, the following guidance should be followed:

- The investigational product infusion should be slowed down (for example, reduce infusion rate by 50% [for example, an infusion rate of 12 mL/h becomes 6 mL/h or slower]) or stopped, depending on the symptoms/signs present:
  - if slowed down, the infusion should be completed at the slower rate, as tolerated

- if determined by the investigator that the infusion should no longer continue, no further attempts to dose the subject should be made
- Supportive care should be employed in accordance with the symptoms/signs

### **7.5. Preparation/Handling/Storage/Accountability**

The investigator or designee must confirm that appropriate temperature conditions have been maintained, as communicated by the sponsor, during transit for all investigational products received and any discrepancies are reported and resolved before use of the study treatment.

Only participants enrolled in the study may receive investigational products or study materials, and only authorized site staff may supply or administer investigational products. All investigational products should be stored in an environmentally controlled and monitored (manual or automated) area in accordance with the labeled storage conditions with access limited to the investigator and authorized site staff.

The investigator, institution, or the head of the medical institution (where applicable) is responsible for study treatment accountability, reconciliation, and record maintenance (such as receipt, reconciliation, and final disposition records).

### **7.6. Treatment Compliance**

The investigational product will be administered at the clinical site, and documentation of treatment administration will occur at the site.

Subjects who are significantly noncompliant (missed at least 1 dose of study drug) will be discontinued from the study.

### **7.7. Concomitant Therapy**

Lipid-lowering drugs (Section 6.2, Criterion [13]) and drugs potentially expected to decrease the heart rate (Table GZEA.4) are not allowed during the study. In general, concomitant medication should be avoided; however, acetaminophen (1 g, maximum 3 g/24 hours) may be administered at the discretion of the investigator for treatment of headaches etc. Additional drugs are to be avoided during the study unless required to treat an AE or for the treatment of an ongoing medical problem (for example, estrogen/progesterone as hormone replacement therapy and thyroid medications). If the need for concomitant medication arises, inclusion or continuation of the subject may be at the discretion of the investigator in consultation with a Lilly CP or CRP. Any additional medication used during the course of the study must be documented.

### **7.8. Treatment after the End of the Study**

Not applicable.

## 8. Discontinuation Criteria

Subjects discontinuing prematurely from the treatment or from the study for any reason should complete AE and other follow-up procedures per the Schedule of Activities (Section 2) of this protocol.

### 8.1. Discontinuation from Study Treatment

Not applicable for this the study.

#### 8.1.1. *Discontinuation of Inadvertently Enrolled Subjects*

If the sponsor or investigator identifies a subject who did not meet enrollment criteria and was inadvertently enrolled, a discussion must occur between the Lilly CP and the investigator to determine if the subject may continue in the study. If both agree it is medically appropriate to continue, the investigator must obtain documented approval from the Lilly CP to allow the inadvertently enrolled subject to continue in the study with or without continued treatment with investigational product.

### 8.2. Discontinuation from the Study

Subjects will be discontinued under the following circumstances:

- Enrollment in any other clinical study involving an investigational product or enrollment in any other type of medical research judged not to be scientifically or medically compatible with this study
- Participation in the study needs to be stopped for medical, safety, regulatory, or other reasons consistent with applicable laws, regulations, and good clinical practice
- Investigator Decision
  - the investigator decides that the subject should be discontinued from the study
  - if the subject, for any reason, requires treatment with another therapeutic agent that has been demonstrated to be effective for treatment of the study indication, discontinuation from the study occurs prior to introduction of the new agent
- Subject Decision
  - the subject, or legal representative, requests to be withdrawn from the study.

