| Single-lead telemetry     |                   | X  | X                | X | X | X | X | X | X | X |        |        |        |        |        |           |    | Day 5 through 8 are SC only. Telemetry is continuous from 12 h predose to 72 h postdose (IV cohorts) or 168 h postdose (SC cohorts). |
| Seated PR                 | X                 | X  | X                | X | X | X | X | X | X | X | X      | X      | X      | X      | X      | X         | X  | Day 1: Within 1 h before dosing and 5 to 15 min, 1 h (+ 30 min), and 8 h after starting dosing; Days 5-7 for SC cohorts only         |
| Body temperature          | X                 | X  | P                | X | X | X |   |   |   | X | X      | X      | X      |        |        | X         | X  | Any time before breakfast                                                                                                            |
| Seated BP                 | X                 | X  | X                |   |   |   |   |   |   |   |        | X      |        | X      |        | X         | X  | Day 1: 5 to 15 min and 1 h (+ 30 min) after starting dosing                                                                          |
| AOBPM                     |                   |    | P, 6 h           | X | X | X | X | X | X | X | X      |        | X      |        | X      |           |    | Days 5 through 7 are SC only. See Section 9.4.2. for more details.                                                                   |
| Adverse event reporting   | X                 | X  | ←-----→          |   |   |   |   |   |   |   |        |        |        |        |        | X         |    |                                                                                                                                      |

| Procedure               | Screening         |    | Treatment Period |   |   |   |   |   |   |        |        |        |        |        |        | Follow-up | ET | Notes |
|-------------------------|-------------------|----|------------------|---|---|---|---|---|---|--------|--------|--------|--------|--------|--------|-----------|----|-------|
|                         |                   |    | Week 1           |   |   |   |   |   |   | Week 2 | Week 3 | Week 4 | Week 5 | Week 7 | Week 9 | Week 13   |    |       |
| Day                     | Day -28 to Day -2 | -1 | 1                | 2 | 3 | 4 | 5 | 6 | 7 | 8      | 15 ±2  | 22 ±2  | 29 ±2  | 43 ±5  | 57 ±5  | 85 ±5     |    |       |

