#### 3.3. Benefit/Risk Assessment

LY3475766 has not been administered to humans. The nonclinical safety information for LY3475766 supports the transition from preclinical status to clinical development. Based on the mechanism of action and nonclinical data, LY3475766 is not considered to be a high uncertainty compound. The only potential risk that is anticipated relates to the finding of a nondose-dependent decrease in heart rate in a 1-month Good Laboratory Practice toxicology study that was performed in cynomolgus monkeys; there were no adverse events (AEs) or any significant electrocardiogram (ECG) findings associated with the decrease in heart rate. Refer to the IB for LY3475766 for more details. This risk is considered to be monitorable and manageable at the planned doses of 10 mg, 30 mg, and 1000 mg IV and 100 mg, 300 mg, and 600 mg SC for LY3475766 in dyslipidemic but otherwise healthy subjects.

More information about the known and expected benefits, risks, serious adverse events (SAEs), and reasonably anticipated AEs of LY3475766 can be found in the IB.

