### 9.2. Adverse Events

Investigators are responsible for monitoring the safety of subjects who have entered this study and for alerting Lilly or its designee to any event that seems unusual, even if this event may be considered an unanticipated benefit to the subject.

The investigator is responsible for the appropriate medical care of subjects during the study.

Investigators must document their review of each laboratory safety report.

The investigator remains responsible for following, through an appropriate health care option, AEs that are serious or otherwise medically important, considered related to the investigational product or the study, or that caused the subject to discontinue the investigational product before completing the study. The subject should be followed up until the event resolves, stabilizes with appropriate diagnostic evaluation, or is reasonably explained. The frequency of follow-up evaluations of the AE is left to the discretion of the investigator.

The investigator will record all relevant AE and SAE information in the eCRF. After the ICF is signed, study site personnel will record, via eCRF, the occurrence and nature of each subject's preexisting conditions, including clinically significant signs and symptoms of the disease under treatment in the study. Additionally, site personnel will record any change in the condition(s) and the occurrence and nature of any AEs.

The investigator will interpret and document whether or not an AE has a reasonable possibility of being related to study treatment or a study procedure, taking into account the disease, concomitant treatment, or pathologies.

A "reasonable possibility" means that there is a potential cause and effect relationship between the investigational product and/or study procedure and the AE.

Planned surgeries should not be reported as AEs, unless the underlying medical condition has worsened during the course of the study.

If a subject's investigational product is discontinued as a result of an AE, study site personnel must report this to Lilly or its designee via eCRF.

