### **9.5.4 Vital signs**

Automated office blood pressure monitoring data (AOBPM) (systolic blood pressure, diastolic blood pressure and pulse rate) will be recorded. Four records are recorded, the first is discarded and for the latter 3 records, the mean will be calculated and used for reporting and analysing.

Vital signs data and AOBPM data will be summarized by treatment and timepoint together with changes from baseline, where baseline is defined as the Day 1 predose assessment. Figures of

mean vital signs and mean changes from baseline profiles over time will be presented by treatment.

Values for individual subjects will be listed.

The relationship between time-matched systolic blood pressure, diastolic blood pressure, and heart rate from AOBPM data and the LY3475766 PK concentration will be evaluated graphically using a scatter plot. The plot will include a longitudinal linear model with independent variables, PK concentration as a continuous variable and time relative to the first dose time as a categorical variable. A compound-symmetry variance-covariance structure will be used to model the within-subject correlation. If the model fails to converge, an alternative structure will be investigated instead. The estimated regression line and associated 90% CI will be fitted on the plot and the p-value for the slope reported.

Example of SAS code as follows.

```
proc mixed data=xxx;  
class time subject;  
model vital = pk_conc time /residual ddfm=kr;  
repeated time / subject=subject type=cs alpha=0.1;  
run;
```

For the AOPBM data, a repeated-measures statistical analysis of absolute and change from baseline vital sign measurements will be produced with fixed effects for treatment, timepoint, and the interaction treatment and timepoint and baseline as a covariate (for the change from baseline analysis). An unstructured covariance structure will be used and a compound symmetric structure can be used if the model fails to converge. The primary contrasts of interest are each dose level versus placebo at each timepoint. Least squares means as well as a 90% CI of the mean difference between each dose level and placebo will be obtained.

Example of SAS code as follows.

```
proc mixed data=xxx;  
class treatment;  
model change = baseline treatment timepoint treatment*timepoint  
/residual ddfm=kr;  
repeated timepoint / subject=subject type=UN;  
lsmeans treatment*timepoint / cl pdiff alpha=0.1;  
ods output lsmeans=lsm diffs=estims;  
run;
```

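### Section 8.2 ends observation of a dosed subject who needs an effective agent, although no dosing is left to stop

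*Combined protocol and SAP*

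**What the plan says.** Every subject has a single dose on Day 1 and about 84 days of follow-up (protocol Sections 1 and 2). Section 8.1, on stopping study treatment, reads "Not applicable for this the study". Section 8.2 lists the circumstances in which subjects will be discontinued from the study. One of them, placed under investigator decisions, is that the subject needs another agent shown to work in the study indication; then "discontinuation from the study occurs prior to introduction of the new agent".

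The lead-in to Section 8 governs what follows: subjects who discontinue early "for any reason should complete AE and other follow-up procedures per the Schedule of Activities". The Schedule (Section 2) has an ET column. It is marked for safety laboratory tests, the lipid panel, ANGPTL3/8, PK, immunogenicity, ECG, seated pulse and seated blood pressure, but not for AOBPM. The note on the AOBPM row, "Days 5 through 7 are SC only. See Section 9.4.2. for more details", deals with cohorts and makes no provision for early termination. Section 9.2.1 releases investigators from actively looking for AEs once a subject has discontinued.

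Section 7.7 bars lipid-lowering drugs. It also leaves continuation of a subject who needs concomitant medication to the investigator, in consultation with the sponsor's physician.

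On risk, Section 3.3 states: "The only potential risk that is anticipated relates to the finding of a nondose-dependent decrease in heart rate". AOBPM carries the modelled heart-rate data. In SAP 9.5.4 the first model concerns "The relationship between time-matched systolic blood pressure, diastolic blood pressure, and heart rate from AOBPM data and the LY3475766 PK concentration". The second is a repeated-measures comparison in which "The primary contrasts of interest are each dose level versus placebo at each timepoint". A further analysis takes each subject's maximum AOBPM value within 3 and within 9 weeks.

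**The concern.** A rule of this kind makes sense in a repeat-dose trial, where it stops dosing before a competing drug starts. Here there is nothing to stop. Once the dose has been given, the only effect of Section 8.2 is to stop watching a person who has received a first-in-human antibody.

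The rule protects lipid values that are secondary or exploratory. It gives up data on the primary objective: the primary endpoints are the incidence of AEs and SAEs and clinically significant changes in vital signs, laboratory values and ECGs. The loss falls most clearly on AOBPM, which feeds the planned analyses of the one anticipated risk and which the ET visit does not contain.

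**Working it through.** The plan gives no figure to reproduce. The check sets the Section 8 text against the Schedule and counts what an affected subject loses.

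**Step 1: what can the rule do?** One dose on Day 1, and Section 8.1 not applicable, mean that no treatment remains after Day 1. The rule can therefore only end observation.

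**Step 2: which follow-up applies after exit?** Section 8 points to the Schedule without saying whether the ET column or the remaining visits are meant. Three things favor one ET visit: the column exists; Section 9.4.6 speaks of a discontinuation visit as the counterpart of the last scheduled assessment; and SAP 9.1 lists data only up to withdrawal. I take the ET-only reading from here on.

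**Step 3: visits lost per affected subject.** Scheduled days are from the Schedule of Activities; ET supplies one of each except AOBPM.

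| Assessment | Scheduled after Day 8 | After Day 29 | At ET |
|---|---|---|---|
| AOBPM | 3 (Days 15, 29, 57) | 1 (Day 57) | 0 |
| PK | 4 (15, 29, 57, 85) | 2 | 1 |
| Immunogenicity | 3 (15, 29, 85) | 1 | 1 |
| Safety laboratory | 5 (15, 29, 43, 57, 85) | 3 | 1 |
| Seated pulse | 6 (15, 22, 29, 43, 57, 85) | 3 | 1 |
| Seated BP | 3 (22, 43, 85) | 2 | 1 |
| ECG | 2 (29, 85) | 1 | 1 |

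**Step 4: effect on the concentration model.** Postdose AOBPM readings with a matching PK sample fall at 6 h and on Days 3, 8, 15, 29 and 57, which makes 6 per subject. Assume 6 active subjects per dose (36 active over 6 cohorts).

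- Pairs per arm: 6 × 6 = 36. Loss: 3/36 = 8.3% (exit after Day 8) or 1/36 = 2.8% (after Day 29).
- Pairs over all active subjects: 36 × 6 = 216. Loss: 3/216 = 1.4% or 1/216 = 0.5%.

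**Step 5: effect on dose versus placebo at a lost AOBPM visit.** With a common SD, the standard error is proportional to √(1/n_active + 1/n_placebo). SAP Section 6 pools placebo, so 12 are assumed.

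- Full data: √(1/6 + 1/12) = 0.500.
- One active subject lost: √(1/5 + 1/12) = 0.532; ratio 1.065.
- One placebo subject lost: √(1/6 + 1/11) = 0.508; ratio 1.015.

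These are upper bounds. The repeated-measures model also draws on the subject's earlier readings, and a replacement would restore the arm size.

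**The case against.** *The rule is a legitimate choice.* TG, LDL-C and apoB are the secondary PD endpoints, and leaving before a lipid-lowering drug starts keeps them, and the attribution of AEs, free of confounding. The aim stands. It can be met by censoring the lipid values, without ending safety observation.

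*Section 7.7 already allows discretion.* It does, and the two sections are in tension. But that discretion covers concomitant medication in general, the same section bars lipid-lowering drugs, and the Section 8.2 clause is specific. It probably prevails.

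*The trigger is nearly hypothetical.* Subjects are otherwise healthy, TG is at most 499 mg/dL, and sites are blinded to postbaseline lipids. This largely stands. Section 6.4 admits subjects after washout of excluded drugs, which is a possible route to a restart, but it says nothing about restarting, and no rate is given.

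*Little is lost.* Heart-rate monitoring is densest early: telemetry to 72 h (IV) or 168 h (SC), and AOBPM at 6 h and through Day 8, with a gap on Days 5 to 7 for IV cohorts. Those readings stay in the models. Section 5.2 allows replacement when the exit was not for a safety finding. This stands for precision, but a replacement cannot supply the dosed subject's own late data.

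A reader might infer that safety follow-up simply ends. The documents do not support that. The ET visit has laboratory tests, PK, antibodies, pulse, blood pressure and ECG. Section 9.2 says: "The investigator remains responsible for following, through an appropriate health care option, AEs that are serious or otherwise medically important", and it extends this to related events. Section 9.4.6 asks sites to try to contact subjects for antibody follow-up.

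A reader might also infer that lipid values drawn under the new agent will enter the SAP 9.4.1 models. That needs the full Schedule to continue after discontinuation, which is the weaker reading (step 2). The missing choice between ET and the remaining visits is a gap in detail, not a present contamination problem.

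**Conclusion.** The point holds as a low-priority, inexpensive improvement. Section 8.2 takes a dosed subject out of the study when no dosing is left to stop. On the natural ET-only reading, that costs the later safety, PK and antibody visits, active AE seeking, and all remaining AOBPM.

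Per affected subject, three AOBPM visits are lost after an exit just past Day 8, or one after an exit just past Day 29. At a lost visit the standard error rises by at most about 6.5% for an active subject or 1.5% for a placebo subject, in a study that is not powered for testing.

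This rests on the ET-only reading, on six active subjects per dose and 12 pooled placebo, on no replacement, and on the AOBPM row as extracted from the Schedule. It also takes agents effective for the study indication, which the protocol does not define, to be mainly lipid-lowering drugs. The number of affected subjects cannot be estimated from the documents and is probably small.

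**What to change.** - **Protocol 8.2:** state that, for a dosed subject, starting an agent effective for the study indication does not end participation. AE, vital-sign, AOBPM, ECG, laboratory, PK and immunogenicity follow-up continues to Day 85 unless the subject withdraws.
- **Protocol 7.7:** add the matching exception to the bar on lipid-lowering drugs.
- **Protocol 8 and Schedule:** for subjects who leave for other reasons, state that the ET visit applies, and add AOBPM to it.
- **SAP 9.4.1:** list and flag lipid and ANGPTL3/8 values from first intake of the agent, set them to missing in summaries and models, and keep earlier values.
- **SAP 9.5:** flag AEs, laboratory values and AOBPM readings after the agent starts, because SAP 9.5.1 counts any new postdose AE as treatment-emergent.

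The SAP 9.4.1 sentence must accompany the protocol change. Once such subjects stay in, up to 6 lipid panels (start just after Day 8) or 3 (just after Day 29) could be drawn under the new agent, and SAP 8 considers deviations only when assigning whole subjects to populations. If the agent lowered a lipid by an assumed 20% to 50%, one uncensored subject would lower the geometric mean of a six-subject arm by 1 − 0.8^(1/6) = 3.7% to 1 − 0.5^(1/6) = 10.9% at those visits. If that subject were one of 12 on placebo, the drug/placebo ratio would rise by 0.8^(−1/12) − 1 = 1.9% to 0.5^(−1/12) − 1 = 5.9%.

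The cost is a few sentences and one mark in the Schedule; the continuing visits are already scheduled. The downside is that some late safety data are collected under a concomitant drug and must be read with the flag, and a few lipid values leave the models.
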